### 2.2. Cognitive Assessments Administered to Assess Self-Regulation

Cognitive assessments are administered remotely using the Inquisit platform by Millisecond [69]. Participants are provided the link to access the platform once they complete the REDCap surveys and are not supervised while they complete their cognitive assessments. Participants are given detailed instructions regarding how to complete the cognitive assessments prior to starting and are provided with contact information to reach research staff if they encounter errors or have questions. Research staff monitor incoming data from the Inquisit platform to track participant completion of the tasks. Inquisit Millisecond has been widely used for online administration of neuropsychological tests (e.g., [70,71,72,73,74,75,76,77,78,79]).

Go/No-Go Task (GNG). The computerized GNG task requires participants to monitor series of stimuli presented in the center of a computer screen and respond as rapidly as possible by pressing a mouse button to respond to target stimuli (Go cues), while withholding a response to non-target stimuli (No-Go cues) [80]. The frequency of Go cues creates a prepotent tendency to respond that must then be inhibited for No-Go cues, which provides a measure of the ability to inhibit a prepotent response [81], with lower scores indicating a greater tendency towards disinhibited behavior. We are currently using this version of the Go/No-Go task in another behavioral trial with individuals in the perinatal period [82].

Stroop Color Word Test. The Stroop Color Word Test is a computerized task in which participants must name the color of a written color word while inhibiting the impulse to read it. The difference between mean response times of correct responses on incongruent and control trials is used to compute an interference score, which provides a measure of attention, with lower scores indicating greater attentional deficits and poorer response inhibition [83]. The Stroop test has been used to assess cognitive functioning in pregnant populations [84,85,86]. 

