Wisconsin Card Sorting Task (WCST). The WCST is a computerized task in which participants must match a target card with one of four category cards under changing conditions. The number of incorrect responses that would have been correct for the preceding condition provides a measure of cognitive inflexibility, with higher scores indicating greater cognitive inflexibility [87]. The WCST has been used to evaluate executive functioning in pregnancy [88].

Delay Discounting Task (DDT). The DDT is a computerized assessment of impulsive decision-making in which participants are presented with a series of monetary values available either immediately or after a temporal delay of varying lengths [89]. Indifference points reflecting the time at which each individual switches from choosing the immediately available value to the delayed value are calculated for each delay interval as the midpoint between the lowest immediate value chosen and the rejected next lowest immediate value [90]. These indifference points are then fit to a hyperbolic function according to the following formula: V = A/(1 + kD), where, V is the value of the indifference point, A is the USD 100 delayed outcome, D is the length of the delay, and k is the magnitude from low to high of the degree to which an individual discounted delayed outcomes [91,92,93]. The DDT has been used to assess impulsivity during the perinatal period [94,95].

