Planned statistical analyses. Prior to hypothesis testing, data will be examined to confirm that the data structure meets analytic assumptions. Aim 1 will be evaluated first by examining the number of individuals who complete screening, calculating the recruitment success rate (the number of participants enrolled divided by the number of those deemed eligible), and evaluating the primary drivers of participant ineligibility by calculating the percentage of those whose participation was discontinued by each reason documented. We will also evaluate retention rates. For the MBCT group, successful retention will be defined in two ways: (1) attending at least four of eight sessions offered, consistent with prior research examining MBCT, including during pregnancy [14,16,17,18], and (2) completing post-intervention assessments. For CAU, successful retention will be operationalized as the completion of post-intervention assessments. Previous mindfulness-based intervention studies conducted during pregnancy have demonstrated >80% retention, so our goal is to match or exceed that (e.g., [16,18,25]). Aim 2 will also be evaluated in several ways. First, baseline to post-intervention change scores will be computed for each measure, and descriptive statistics for each change score will be performed. Data from the SCID will be used to determine rates of psychiatric diagnoses at baseline and three months postpartum, and variables will be constructed to indicate whether individuals with diagnoses identified at baseline continue to meet diagnostic criteria at three months postpartum. To formally explore the effect of the intervention on psychological functioning at three months postpartum, within-subjects repeated measures MANOVAs will be performed with EPDS, PSS, PSWQ, and RRS scores as dependent variables. A logistic regression analysis will also be performed to determine the impact of the intervention on diagnostic status at three months postpartum. To evaluate the preliminary effects on self-regulation at three months postpartum, cognitive scores will first be transformed to z-scores and the average z-score will be calculated to derive a composite self-regulation score at each time point. A within-subjects repeated measures MANOVA will be performed with cognitive z-scores as the dependent variable.

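### The self-regulation composite averages task z-scores that run in opposite directions with no alignment step, and the printed Stroop direction conflicts with the usual meaning of an interference score

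*Protocol article*

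**What the plan says.** The paragraph on planned statistical analyses (end of section 2.3) states the scoring rule for self-regulation: "cognitive scores will first be transformed to z-scores", and then "the average z-score will be calculated to derive a composite self-regulation score at each time point". A repeated measures MANOVA on the cognitive z-scores follows. It is not clear whether this means the composite or the separate tasks.

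Section 2.2 describes the direction of the four task scores:

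- Go/No-Go: "with lower scores indicating a greater tendency towards disinhibited behavior", so higher is better.
- Stroop: "The difference between mean response times of correct responses on incongruent and control trials is used to compute an interference score", "with lower scores indicating greater attentional deficits and poorer response inhibition" (two parts of one sentence), so higher is better as printed. The order of subtraction is not given.
- WCST: "with higher scores indicating greater cognitive inflexibility", so higher is worse.
- Delay discounting: "The DDT is a computerized assessment of impulsive decision-making", and "k is the magnitude from low to high of the degree to which an individual discounted delayed outcomes". A higher k therefore means more impulsive choice, which is worse.

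The article mentions no reversal or alignment of scores.

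**The concern.** Z-scoring removes the units of a score but keeps its direction. If some inputs rise with better performance and others fall, their plain average is a contrast between tasks and not a measure of self-regulation. Its sign then has no clear meaning.

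The Stroop sentence raises a second problem. An interference score built from incongruent and control response times would usually be larger when the conflicting word slows the participant more, that is, when inhibition is poorer. The article says the reverse. This matters even to an analyst who intends to align the tasks, because the printed directions are the natural guide for doing so.

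Self-regulation is one of the two outcome domains in Aim 2, and the Discussion says these analyses prepare a larger trial of self-regulation as a mechanism. A composite that shows nothing, or the wrong sign, could misdirect that decision.

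**Working it through.** The article states no figure for the composite, so there is none to reproduce. The check concerns direction, followed by arithmetic.

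**Inputs from the article.** Task directions from section 2.2; the averaging rule from the planned analyses; 70 participants at equal allocation, so 35 per arm; about 20% attrition, so 35 × 0.8 = 28 per arm; α = 0.05, taken as two-sided. The Emotion Regulation Questionnaire, listed under self-regulation in Table 1, is a questionnaire and is left out of the cognitive composite.

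**Assumptions, not in the article.** Every task truly improves by the same d SD. Tasks correlate equally, with r = 0.2 (range 0 to 0.4). For power, d = 0.5 is illustrative and the arms are compared by a two-sample t-test.

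**Formulas.** Let s = +1 if a task enters with higher = better and -1 if it enters with higher = worse.

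- Composite shift = d × (sum of the four s) / 4.
- Composite variance = [4 + 2r × (sum of s_i s_j over the six pairs)] / 16.

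**Shift** (order: Go/No-Go, Stroop, WCST, k)

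| Case | Signs | Shift |
|---|---|---|
| A. As written, printed Stroop direction true | +, +, -, - | (1+1-1-1)d/4 = 0 |
| B. As written, Stroop incongruent minus control | +, -, -, - | (1-1-1-1)d/4 = -0.5d |
| C. WCST and k reversed, printed direction trusted on an incongruent-minus-control Stroop | +, -, +, + | (1-1+1+1)d/4 = +0.5d |
| D. All aligned | +, +, +, + | +1.0d |

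**Composite SD at r = 0.2.** The pair sums are -2 (A), 0 (B and C) and 6 (D).

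- A: √[(4 - 0.8)/16] = 0.447
- B and C: √(4/16) = 0.500
- D: √[(4 + 2.4)/16] = 0.632

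In composite SD units the effects are 0 (A), -1.0d (B), +1.0d (C) and 1/0.632 = 1.6d (D).

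**Power at d = 0.5, r = 0.2**

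| Case | Standardised effect | 35 per arm | 28 per arm |
|---|---|---|---|
| A | 0 | 5% (= α) | 5% |
| B | -0.50 (wrong sign) | 54% | 45% |
| C | +0.50 | 54% | 45% |
| D | +0.79 | 90% | 83% |

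For r from 0 to 0.4, case D runs from 1.00 down to 0.67, with power from 98% to 79% at 35 per arm and from 96% to 70% at 28. Cases B and C do not depend on r.

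**Stroop direction, with assumed times.** Poor inhibition: 1100 - 800 = 300 ms. Good inhibition: 900 - 800 = 100 ms. On incongruent minus control, lower is better, against the printed sentence. On control minus incongruent the values are -300 and -100, and the printed sentence is right. The composite then still cancels, as in case A, unless WCST and k are reversed.

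**Unequal effects.** In case A the shift is (Go/No-Go + Stroop - WCST - k)/4 in the separate task improvements. It is zero only when the two pairs balance, but it is always a difference and never a sum.

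**Separate tasks.** A multivariate test does not depend on the sign of its inputs. In one simulated data set with four tasks and 35 per arm, Hotelling's T² was 24.97 both before and after three tasks were flipped.

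**Standardisation.** If z-scores are taken within each visit, the whole-sample mean is 0 at every visit with complete data, so the overall time effect is zero by construction. The difference between arms at each visit, and hence the group-by-time contrast, remains free.

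**The case against.** The strongest reply is that an article condenses its full protocol. Reverse-coding before averaging is a routine step that an analysis plan not shown may contain, and the authors describe each score closely enough to be aware of its polarity. This stands in part: nobody can say from the article that the scores will be left unaligned. But the article does not leave the composite open. It states a rule, and that rule gives a wrong score if followed. Alignment guided by the printed Stroop direction could also still leave one task with the wrong sign (case C).

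A reader might infer more than the text supports on four points:

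- *A real benefit is bound to vanish or appear as harm.* Exact cancellation needs equal effects on all tasks, and the reversed sign needs Stroop to be incongruent minus control. Neither is stated.
- *The Stroop direction is certainly backwards.* The article says only that a difference is used to compute the score. The conflict rests on the usual reading of interference.
- *The composite is the only view of self-regulation.* Change scores from baseline to post-intervention are planned for each measure, confidence intervals and effect sizes are promised for cognitive outcomes, and the MANOVA may use the separate tasks. The change scores, however, do not cover three months postpartum, and an effect size for the composite does depend on sign.
- *Standardisation removes the treatment comparison.* Within-visit z-scoring is one reading among several, and it would remove only the overall time effect.

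**Conclusion.** Wrong as written, and a moderate correction. The stated rule averages scores that the article itself describes as running in opposite directions. With equal improvement of d SD on all four tasks, the composite shifts by 0 or -0.5d, depending on how Stroop is subtracted, instead of +1.0d. With WCST and k reversed but the printed Stroop direction trusted on an incongruent-minus-control score, it shifts by +0.5d, half the aligned value.

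The opposing directions of Go/No-Go and WCST are explicit in the article, and that of k follows from its description. The sizes rest on the equal-effects assumption, and the power figures also on the assumed d and r.

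A reader might take this as a threat to the trial. The documents do not support that: feasibility and acceptability are the primary focus, the cognitive analyses are declared preliminary, and scoring can be corrected before analysis without loss of data.

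**What to change.** 1. In section 2.2, state the Stroop subtraction order and make the stated direction match it.
2. In the planned analyses, say that every task is coded so that higher means better self-regulation before averaging: reverse WCST errors and k, and reverse Stroop if it is incongruent minus control. A log transform of k is optional and not part of this error.
3. State whether the MANOVA uses the aligned composite or the separate task z-scores. If it uses the composite, report the aligned tasks beside it at each visit.
4. Standardise all visits to the baseline mean and SD, so that the overall time effect, which the Discussion wants to describe, can be estimated.

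The cost is a few sentences of wording. No new data, visits or participants are needed.

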### 2.1. Self-Report and Interview-Based Measures

Depressive symptoms. The presence and severity of depressive symptoms are measured using the 10-item Edinburgh Postnatal Depression Scale (EPDS; [36,37]), which is a widely used instrument validated in pregnancy and the postpartum period [38,39]. Participants rate the severity of depressive symptoms experienced in the past week on a Likert scale ranging from 0 to 3. Scores are summed up to form a total score, with higher scores reflecting more severe symptomatology. The EPDS has demonstrated adequate internal consistency in prior research (Cronbach’s α = 0.77; [37]).

Perceived stress. Perceptions of daily life stress are measured using the Perceived Stress Scale (PSS; [40]). This 10-item questionnaire asks participants to rate items on a 5-point Likert scale from 0 (never) to 4 (very often) on how overwhelming, unpredictable, or uncontrollable they find their lives. Responses are summed up to form a total score, with higher scores indicating greater perceived stress. This scale has been shown to exhibit satisfactory reliability (Cronbach’s α = 0.85) and validity [41], including during the perinatal period [42].

Generalized worry. Symptoms of generalized worry are assessed using the 16-item Penn State Worry Questionnaire (PSWQ; [43,44]). Participants rate each item on a 5-point Likert scale from 1 (not at all typical of me) to 5 (very typical of me). Higher scores are indicative of more severe worry. The instrument has satisfactory internal consistency and construct validity [45], including among individuals evaluated during pregnancy or the postpartum period [46].

Rumination. Participants complete the Ruminative Responses Scale (RRS; [47]), a 22-item scale assessing the tendency to engage in a negative, self-focused thinking style in response to negative experiences. Participants rate each item on a 4-point Likert scale ranging from 1 (never) to 4 (always). A higher score indicates a higher degree of ruminative symptoms. The RRS has been shown to possess adequate internal consistency and convergent validity [48,49], including during the perinatal period [50].

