Sample size estimation. Because this is a pilot investigation focused on outcomes that have been under-investigated in previous trials of MBCT during the perinatal period, our primary focus is demonstrating feasibility and acceptability, and all analyses conducted to evaluate he effects of MBCT on psychological and cognitive outcomes are therefore considered preliminary. Nevertheless, we include an estimation of the sample size needed based on the power to detect differences between MBCT and CAU in depressive symptoms following the eight-week treatment period. We selected depressive symptoms as the outcome to use for sample size estimation because, compared with other psychological outcomes of interest measured in this study, the impact of MBCT on depressive symptoms is well-established. The estimated effect size is 0.71 based on the results of a recently published meta-analysis of randomized controlled trials of MBCT among individuals with current depressive symptoms [97]. Assuming an 80% power and α of 0.05, we determined that a sample size of 72 (36 per group) would be necessary to detect a treatment effect on continuously measured depressive symptoms. Therefore, our planned sample of 70 individuals would be adequate to evaluate this effect. However, given the likely attrition rate of ~20%, we will also examine confidence intervals and effect sizes when evaluating the impact of MBCT on psychological and cognitive outcomes [98].

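### The sample size rests on an end-of-treatment comparison of depressive symptoms, but the analysis section names no between-arm analysis for that visit and words its formal tests around three months postpartum

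*Protocol article*

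**What the plan says.** All references are to the protocol article.

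- **Sample size (section 2.3, sample-size paragraph).** The calculation is "based on the power to detect differences between MBCT and CAU in depressive symptoms following the eight-week treatment period". Its inputs are given as "The estimated effect size is 0.71 based on the results of a recently published meta-analysis of randomized controlled trials of MBCT" and "Assuming an 80% power and α of 0.05". The result is that "a sample size of 72 (36 per group) would be necessary to detect a treatment effect on continuously measured depressive symptoms", and the paragraph concludes that "our planned sample of 70 individuals would be adequate to evaluate this effect".
- **Instrument (section 2.1).** The sample-size paragraph does not name a scale. Section 2.1 says that "depressive symptoms are measured using the 10-item Edinburgh Postnatal Depression Scale", and no other depressive-symptom scale is listed, so EPDS is the natural reading.
- **Post-intervention visit (section 2.3, planned statistical analyses).** For Aim 2, "baseline to post-intervention change scores will be computed for each measure, and descriptive statistics for each change score will be performed". No between-arm analysis of these scores is named.
- **Formal analyses (same paragraph).** "To formally explore the effect of the intervention on psychological functioning at three months postpartum", repeated-measures MANOVAs are planned on EPDS, PSS, PSWQ and RRS. A logistic regression on diagnostic status and a MANOVA on cognitive z-scores are also tied to three months postpartum. Aim 2 in the Introduction names the same visit.
- **Status.** The sample-size paragraph puts feasibility and acceptability first and calls all efficacy analyses preliminary. Because about 20% attrition is expected, it adds that confidence intervals and effect sizes will be examined.

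**The concern.** A power calculation describes one comparison: an outcome, a visit and a test. Here it describes depressive symptoms in two arms at the end of treatment. The adjacent paragraph on analyses gives that visit descriptive statistics only and sets its inferential work at a different visit, mostly on several outcomes jointly. A reader who wants the result that the 70 participants are said to be adequate for cannot tell which planned analysis delivers it.

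The cost is interpretive. The article says that the trial will be a basis for a larger one, and the end-of-treatment EPDS difference with its interval is the result that can be set directly against the assumed 0.71. Without a named contrast, how it is estimated (raw follow-up score, change score or baseline-adjusted) stays open until the data are in.

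**Working it through.** **1. The stated figure.** Inputs from the sample-size paragraph: d = 0.71, power 80%, α = 0.05 (two-sided assumed; sidedness is not stated), 1:1 allocation.

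n per arm = 2(z₀.₉₇₅ + z₀.₈₀)² / d² = 2(1.960 + 0.842)² / 0.71² = 31.1, so 32 per arm, 64 in total. The t-test calculation gives 32.1, so 33 per arm, 66 in total. The stated 72 is not reproduced. That is a separate matter and does not affect this point, which concerns the comparison that was sized and not the count.

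**2. What was sized against what is analysed.**

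| | Sample-size paragraph | Planned analyses, post-intervention | Planned analyses, formal |
|---|---|---|---|
| Visit | End of eight-week treatment | End of eight-week treatment | Three months postpartum |
| Outcome | Depressive symptoms alone | Each measure | Four scales jointly; diagnosis; cognitive z-scores |
| Comparison | MBCT versus CAU | Not named | Effect of the intervention |
| Method | Two groups, continuous outcome | Descriptive change scores | MANOVA; logistic regression; MANOVA |

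No column to the right of the first matches it in visit, outcome and comparison together.

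**3. The two visits are well apart.** Enrolment is at 12 to 30 weeks of gestation. Adding 8 weeks, the course ends at weeks 20 to 38. With birth assumed at week 40, three months postpartum is about week 40 + 13 = 53. The gap is 53 − 38 = 15 to 53 − 20 = 33 weeks, with the birth in between. Waiting for a cohort to fill would shorten it.

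**4. A joint test is not the sized test.** As an illustration, take a single-visit between-group Hotelling test on four outcomes with 28 per arm. Assume an effect of 0.71 on all four and a common correlation of 0.3 to 0.7. Power is then 85% down to 62%, against 74% for the two-group test on one outcome. The assumptions are not in the article; the figures only show that the two tests have different power.

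**5. Power of the contrast that would match.** Completers per arm: 70 × (1 − 0.20) / 2 = 28.

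- Unadjusted: noncentrality = d√(n/2) = 0.71 × √14 = 2.66. Two-sided t-test power is 74.2% (normal approximation 75.7%). With all 35 per arm it is 83.3%.
- Adjusted for baseline EPDS, with r the correlation of baseline and follow-up: effective d = 0.71 / √(1 − r²). At r = 0.5 this is 0.71 / 0.866 = 0.820, and power is 85.4%.
- The article gives no r. At 28 per arm, r = 0.3 gives d = 0.71 / √0.91 = 0.744 and power 78%; r = 0.7 gives d = 0.71 / √0.51 = 0.994 and power 95%.

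The drop from 83% to 74% comes from attrition at an unchanged effect. It is not caused by the mismatch of visits.

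**The case against.** Several stronger readings are tempting, and the article does not support them.

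- **That the end-of-treatment comparison is never tested.** EPDS is collected at all three visits (Table 1) and is a dependent variable in a repeated-measures MANOVA whose time levels are not listed. The post-treatment visit may be one of them, and listing levels and follow-up contrasts is often left to a fuller document. What stands is narrower: no such contrast is named, the stated purpose is the three-month effect, and a joint four-outcome test would still not be the comparison that was sized.
- **That no between-arm estimate will exist.** The sample-size paragraph promises confidence intervals and effect sizes for the impact of MBCT, without limiting this to a visit. That may cover the end of treatment. It fixes neither the visit nor the estimator.
- **That 80% power is claimed at three months.** It is not. The paragraph ties the figure to the end of treatment and calls 70 adequate for that effect only.
- **That the three-month analyses should be relabelled exploratory.** The aims, the analysis paragraph and the sample-size paragraph already describe them as exploratory or preliminary, and a pilot need not give power for every exploratory analysis.
- **That three-month power is a known low figure.** At 28 per arm it would be 45% for an effect of 0.5 and 31% for 0.4, but the article gives no three-month effect. These are illustrations and do not measure a defect.

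It is also fair to say that baseline adjustment is an analyst's choice in a trial led by feasibility. It is still the more precise choice for data that will be collected anyway.

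**Conclusion.** The point holds in limited form. The sample size is based on a between-arm difference in depressive symptoms at the end of treatment, and the analysis paragraph names no between-arm analysis for that visit. Its formal analyses are worded around three months postpartum. This rests on the text of two adjacent paragraphs and one inference, that depressive symptoms means EPDS.

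The weight is modest: feasibility leads, efficacy is labelled preliminary, and no power claim is made for the later visit. A matching contrast with 28 completers per arm and d = 0.71 would have about 74% power unadjusted. Adjusted for baseline it would have about 85% at an assumed correlation of 0.5, or 78% to 95% for correlations of 0.3 to 0.7.

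**What to change.** 1. In the planned analyses, specify a between-arm EPDS contrast at the post-intervention visit, adjusted for baseline EPDS, with a 95% confidence interval, as the analysis that corresponds to the sample-size paragraph. The descriptive change scores can stay beside it.
2. In the sample-size paragraph, name EPDS and add one sentence: the 80% power figure applies to that contrast only and not to the three-month analyses.

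The cost is one model and one sentence. EPDS is already scheduled at baseline and post-treatment, so no new data, visits or participants are needed. Recruitment is described as ongoing, so the contrast should be fixed before outcome data are compared by arm.

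### The sample of 70 is called adequate for 80% power, but the plan's own 15–20% attrition leaves about 56–60 analysed and 74–77% power, and the stated requirement of 72 does not follow from the stated inputs

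*Protocol article*

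**What the plan says.** All the relevant statements stand in the Sample size estimation paragraph at the end of section 2.3 of the Protocol article, with support from three other paragraphs.

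- Target of the calculation: the "power to detect differences between MBCT and CAU in depressive symptoms following the eight-week treatment period".
- Effect size: "The estimated effect size is 0.71 based on the results of a recently published meta-analysis of randomized controlled trials of MBCT".
- Error rates: "Assuming an 80% power and α of 0.05". The test, its sidedness and the type of effect size are not given.
- Requirement: "we determined that a sample size of 72 (36 per group) would be necessary to detect a treatment effect on continuously measured depressive symptoms".
- Conclusion, in the next sentence: "Therefore, our planned sample of 70 individuals would be adequate to evaluate this effect".
- Attrition, in the sentence after that: "given the likely attrition rate of ~20" percent. The only response is to report effect sizes with confidence intervals as well.

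The Participant attrition paragraph gives about 15–20% from earlier trials of mindfulness-based interventions in pregnancy. The Randomization paragraph gives equal allocation. The Planned statistical analyses paragraph sets a retention goal of matching or exceeding the more than 80% seen in earlier studies. The sample size paragraph itself says that feasibility and acceptability come first and that the efficacy analyses are preliminary.

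**The concern.** Three consecutive sentences do not fit together. A number is called necessary, a smaller number is called adequate on the strength of it, and a likely loss of one fifth of participants is then mentioned without entering the number. The required number also cannot be recovered from the inputs given beside it.

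What is at stake is the accuracy of a power statement that the authors chose to make. A reader who takes it at face value will believe that the trial has at least 80% power for an effect of 0.71 on depressive symptoms at the end of treatment. At the number of participants the article itself expects to retain, it does not. The article presents the pilot as the basis for a larger trial, so a calculation that cannot be reproduced may also be carried forward.

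**Working it through.** **Inputs from the article.** Effect size 0.71; power 0.80; alpha 0.05; 1:1 allocation; 70 planned; 15–20% attrition.

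**Assumptions.** Two-sided test, two-sample t-test at the end of treatment, 0.71 as a standardised mean difference, equal arms.

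**Step 1: try to reproduce 72.** The normal approximation per group is

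n = 2(z₀.₉₇₅ + z₀.₈₀)² / d² = 2(1.960 + 0.842)² / 0.71² = 15.70 / 0.5041 = 31.1, rounded up to 32 (64 in total).

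The exact noncentral t calculation gives 32.13, rounded up to 33 (66 in total). The article's 36 per group is therefore not reproduced; at 36 per group the power is 84.4%. A one-sided test needs about 25–26 per group (50–52 in total), which is further from 72.

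**Step 2: look for inputs that would give about 72.**

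| Change to the inputs | Total |
|---|---|
| 66 inflated for 20% attrition: 66/0.80 | 83 |
| 66 inflated for 15% attrition: 66/0.85 | 78 |
| 64 inflated for 20% or 15% attrition | 80 or 76 |
| 64 inflated for 10% attrition: 64/0.90 | 72 |
| Power about 85% instead of 80% | 72–74 |
| Effect size 0.67 instead of 0.71 | 72 |
| Allowance for a rank test | about 68–70 |

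The routes that reach 72 all need a value the article does not state. At the article's own attrition rates, 72 is not an inflated figure. It is therefore reasonable to read 72 as the number to be analysed, although the article does not use that word.

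**Step 3: expected number analysed.**

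- 20% attrition: 70 × 0.80 = 56, or 28 per arm.
- 15% attrition: 70 × 0.85 = 59.5, about 60, or 30 per arm.

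**Step 4: power at d = 0.71, two-sided 0.05.** The noncentrality parameter is δ = d√(n/2), with 2n − 2 degrees of freedom. For n = 28, δ = 0.71 × √14 = 2.66 with 54 degrees of freedom.

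| Per arm | Situation | Power (t-test) |
|---|---|---|
| 36 | the stated requirement | 84.4% |
| 35 | 70 with no attrition | 83.3% |
| 33 | the recomputed requirement | 81.1% |
| 30 | about 15% attrition | 77.2% |
| 28 | 20% attrition | 74.2% |

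The normal approximation at 28 per arm gives 75.7%, so the conclusion does not depend on the choice of formula.

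**Step 5: detectable effect.** With 28 per arm, 80% power needs d = 0.76, which is above the assumed 0.71.

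**The case against.** The strongest case on the other side is that this is a pilot. Feasibility and acceptability are declared primary, the efficacy analyses are labelled preliminary, and the Discussion defers to a larger, fully powered trial. The shortfall is about 6 percentage points at 20% attrition and about 3 at 15%, and if the retention goal is met 74% is roughly the floor. The article also answers attrition with interval estimates, which is good practice and guards against reading a null result as no effect. All of this stands and limits the severity. It does not make the adequacy claim true.

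The sidedness and the type of effect size are unstated. A one-sided test would give 84% power with 56 analysed. But it would need only 50–52, which makes the stated 72 harder to explain. A condensed article may also have dropped an input, such as a 10% dropout allowance. That would explain the 72 but would conflict with the roughly 20% given two sentences later.

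A reader might infer more than the article supports:

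- **That the trial is underpowered because 70 is below 72.** The sentences do conflict, but 72 is larger than the stated inputs require, and 70 without losses would have 83% power. Attrition is the cause of the shortfall.
- **That 90 should have been randomised (72/0.80).** This inflates a figure that cannot be reproduced. From 66, the number is 83, or 84 for equal arms.
- **That the true effect must be smaller here.** The 0.71 comes from a "meta-analysis of randomized controlled trials of MBCT among individuals with current depressive symptoms", while this trial also admits people on the perceived stress score alone. But the article describes symptoms from mild to severe, and the cited source is not available, so the size of any difference cannot be established.
- **That baseline adjustment rescues the claim.** At an assumed baseline correlation of 0.5 it would give about 85% with 28 per arm. The planned analyses are change-score summaries and repeated measures MANOVAs, with no baseline-adjusted comparison, and the correlation has no source. A simple change-score comparison at the same correlation would leave power at 74%.

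**Conclusion.** The point holds: the power statement is wrong as written and should be corrected. On the stated inputs, 66 analysed are needed, not 72. The 70 planned would suffice only if almost nobody were lost. At the article's own attrition, 56 to 60 are expected and power is about 74% to 77% for an effect of 0.71, with a detectable effect of 0.76 at 28 per arm.

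The result assumes a two-sided two-sample t-test on a standardised mean difference with equal arms. The size is modest, and no feasibility conclusion depends on it. That a null result on depressive symptoms would be misread is a possibility, not something the article invites, given its own caveats.

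**What to change.** Keep the planned 70 and rewrite the paragraph:

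1. Name the test, its sidedness and the type of effect size.
2. Correct 72 to 66 analysed (33 per group), or state the input that produces 72 and reconcile it with the attrition rate.
3. Replace the adequacy claim with wording such as: about 66 participants analysed would give 80% power for a standardised difference of 0.71; with 70 randomised and 15–20% attrition, about 56–60 are expected, giving about 74–77% power, and less if the true effect is smaller.
4. Keep the commitment to effect sizes with confidence intervals as the main basis for interpretation.

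Do not add a baseline-adjusted power figure unless that analysis is adopted in the plan and the correlation is justified.

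The cost is one reworded paragraph and a less favourable power figure. No extra participants and no change in conduct are needed. Restoring 80% power under the same assumptions at 20% attrition would instead take 66/0.80 = 82.5, so 83 randomised (84 for equal arms), which a pilot of this kind need not do.
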